### Readiness of the Proposed Technology

Telemonitoring has been researched in a wide variety of contexts for the management of chronic diseases [7]. This approach is increasingly being trialed in Canada for chronic disease management but is not yet part of standard of care [8]. Telemonitoring of heart rate, blood pressure, oxygen saturation, and daily body weight using biometric sensors are ready for incorporation into clinical utilization. We will work with TELUS Health, a medium enterprise in health care and one of our technology partners, to scale up and extend the home telemonitoring platform for heart failure in British Columbia.

We will also work with Sentrian, a small enterprise based in Aliso Viejo, California, Unites States, to introduce a predictive analytics platform into TEC4Home to evaluate its readiness in home telemonitoring for commercialization in British Columbia. Predictive analytics is defined as “the practice of extracting information from existing data sets in order to determine patterns and predict future outcomes and trends” [9]. Currently, telemonitoring relies on clinicians to detect data abnormalities from each sensor and interpret the combination of these signals to determine the state of wellness of the patients. Predictive analytics uses computer software to carry out data mining to intelligently screen for abnormal signals, in isolation or in combination, and present these episodes to the clinicians for further interpretation and action. This improves detection and reduces the frequency of false alarms. The Sentrian platform uses machine learning and feedback to animate predictive analysis and improve its accuracy over time [9]; its Remote Patient Intelligence approach can increase the sensitivity of detection of true abnormal events and reduce the incidence of false positive signals, thereby allowing clinicians to appropriately focus their attention on significant events and reduce distractions from false alarms. In May 2015, this technology commenced its journey through a US trial on patients with chronic obstructive pulmonary diseases. In TEC4Home, we will apply Sentrian’s Remote Patient Intelligence platform to test its effectiveness as a software aid to clinicians monitoring patients with heart failure.

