#### The Technology

The TELUS Health Remote Patient Monitoring (RPM) solution has three components: sensors, patient station, and clinician station. The sensors (blood pressure cuff, pulse oximeter, and weight scale), measure patients’ blood pressure, pulse rate, oxygen saturation, and weight and can be self-applied by the patients without help. These sensors collect the patient’s biometric measurements and send the readings to the patient station. The patient station consists of a software application on a mobile tablet that collects sensor data and presents a series of questions to assess presence of any symptoms such as dizziness, shortness of breath, coughing, or swelling. All of the data entered are transmitted to a data hub where the patient’s data is analyzed, collated, and displayed. The clinician station consists of a software application on a mobile tablet or a personal computer that is used by clinicians to view patient data. Alerts are flagged if one or more sensors show biometric data falling outside of the normal range set for the patient or if the patient reports serious problems such as syncope. The monitoring clinicians then decide on and initiate actions accordingly. TELUS Health RPM can be connected by either cellular wireless or broadband Internet, and dial-up Internet access is available if required.

The Sentrian Remote Patient Intelligence platform is incorporated to augment the clinician station software, simultaneously receiving and analyzing sensor signals. Abnormalities detected are flagged by the clinicians, who can then decide upon appropriate actions. These actions are subsequently entered into the software so that over time, machine learning algorithms will be customized to the patient’s own physiologic behaviors, thus resulting in more accurate identification of true abnormalities and a reduction of false alarms.

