#### Process and Outcome Measurement

Our primary and secondary outcomes are aligned with the Triple Aim framework (ie, experience of care, population health, and cost/utilization). The primary outcome will be whether or not a patient returns to an emergency department, is hospitalized, or dies within 90 days following discharge. Secondary outcomes are reduction in cost as compared to usual care, improvement of communication during transition of care, quality of life (QoL), patient experience of care, and reductions in mortality and morbidity. Working with the Patient-Centered Performance Measurement and Improvement team in British Columbia, QoL and Patient-Reported Experience Measures (PREM) will be refined during Study 1.

Additionally, patient and health professional experience and satisfaction will be collected via interviews to gather quality improvement information. For health professionals, this will include gathering perspectives on the perceived impact of the home telemonitoring.

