#### Intervention and Control Population

Study hospitals will be selected and matched with control hospitals in pairs based on the 90-day emergency department revisit or hospital admission rate prior to randomization, emergency department staffing (ie, ratio of certified emergency physicians to family physicians in emergency department workforce, number of individual physicians), service area population, and annual number of emergency department visits. One hospital in each pair will be randomly assigned to receive the TEC4Home intervention and the other will remain with usual care. Hospitals will be matched and randomized within each Health Authority in British Columbia, as each Authority will commence the trial at different times according to the size of the population it serves. Sites in Health Authority groupings will enroll in the 18-month study period (in descending order according to size of population served) at the beginning of each subsequent month. At the end of each Authority’s 18-month trial period, emergency departments will participate in an additional total 90 days of monitoring (60 days) and follow-up (30 days) to ensure complete data is gathered for any patients enrolled within the last month of the study period. The intent of this approach is to maximize geographic balance for both equitable opportunity and generalizability purposes. Hospitals for which no appropriate match can be identified will be excluded.

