#### Process and Outcome Measurement

For both the feasibility study (Study 1) and cluster RCT (Study 2), the primary outcome goal is to reduce emergency department revisits/admissions measured by the proportion of patients who have an emergency department visit or admission within 90 days following discharge. This will be measured via hospital data and patient self-report postintervention. This aligns with the Triple Aim goal of improving population health [24]. Secondary outcomes related to the Triple Aim goal of cost effectiveness are reduction in cost as compared to usual care measured by utilization relative to patient outcomes and experience measured via hospital data as well as patient self-report. Reduction in cost metrics to ascertain cost utility (ie, number of emergency department visits saved; quality-adjusted life years) will be assessed via PROM including QoL measure. Outcomes related to the Triple Aim goal of improved patient experience of care are improved QoL for heart failure patients and improved experience of care (eg, continuity of care, comfort) as measured by the PREM tool. Other population health-related outcomes include reduction in mortality as measured by hospital data and reduction in morbidity as tracked through patient sensor data and self-report.

Primary and secondary outcomes will be identical to the feasibility study. The primary outcome will be whether or not a patient returns to an emergency department, is hospitalized, or dies within 90 days following discharge (60 days of which the patient will be monitored). Utilization data (eg, emergency department visits and admissions) will be assessed by accessing hospital and provincial database records as well as through patient self-reporting of utilization after the study period; the former is the primary method, and the latter will be considered in sensitivity analysis.

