#### Data Collection Procedures

Both control and intervention patients will complete pre- and poststudy period surveys as described in Study 1. The ultimate primary and secondary outcomes will be subject to further development and refinement as necessary by the project team as informed by the feasibility study. Patient screening and training to use the TEC4Home system will occur as in the feasibility study. Patients will be monitored at home for one month during which data will be collected daily from the patient station biosensors (eg, blood pressure) and self-reported health indicators (eg, dizziness). Pre- and postintervention surveys will be administered to patients, recording social demographics and QoL as measured by the PROM and PREM tools. Postsurveys will include self-report items related to health system utilization including family physician visits, emergency department visits, and lab work.

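### In the cluster RCT, the secondary outcome of reduced morbidity relies partly on home sensor data that only the intervention arm can supply, so that part cannot be compared with usual care

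*Protocol article*

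**What the plan says.** All references are to the protocol article.

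- **Status of the outcome.** Study 1, Process and Outcome Measurement, includes among the secondary outcomes "patient experience of care, and reductions in mortality and morbidity". The section of the same name under Study 2 states "Primary and secondary outcomes will be identical to the feasibility study".
- **Source of the data.** That Study 2 section, in a paragraph that covers both the feasibility study and the cluster RCT, gives the morbidity outcome as "reduction in morbidity as tracked through patient sensor data and self-report".
- **Control condition.** Intervention and Control Population: "One hospital in each pair will be randomly assigned to receive the TEC4Home intervention and the other will remain with usual care". Readiness of the Proposed Technology says of telemonitoring in Canada that it "is not yet part of standard of care". The Cost-Effectiveness Evaluation treats the platform as a cost added to usual care.
- **Where sensor and symptom data arise.** The Technology describes a tablet-based patient station that "collects sensor data and presents a series of questions to assess presence of any symptoms". Data Collection Procedures (Study 2) has biosensor readings and self-reported indicators collected daily from patients while they are monitored at home.
- **What both arms supply.** Data Collection Procedures (Study 2): "Both control and intervention patients will complete pre- and poststudy period surveys as described in Study 1".
- **Planned use of monitoring data.** Analysis (Study 2) assigns them to statistical process control charts and mentions no comparison between arms.

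**The concern.** A reduction in an outcome of a randomised trial means a reduction relative to control. The named source for morbidity is one that control patients do not have. The definition suits the feasibility study, in which every patient is monitored and no control group is described. It was carried into the controlled trial without being adapted.

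Two things could follow if it stays. If morbidity is read from sensor data, the control arm has no observations and there is no contrast to estimate; what remains is a trend within the intervention arm. If sensor findings are combined with self-report, one arm is observed daily with prompted symptom questions while the other is asked in surveys before and after the study period. Any difference then mixes a treatment effect with a difference in detection.

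**Working it through.** **1. The plan's own figure.** The article gives no figure for morbidity. Its only power figure concerns the primary outcome (Power and Sample Size: 12% against 6%, 30 hospitals of 30 patients, intraclass correlation .005, two-sided alpha .05, power 84%).

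- Intraclass correlation from the stated SD: 0.024² / (0.12 × 0.88) = 0.00545, close to the stated .005.
- Design effect: 1 + (30 − 1) × 0.005 = 1.145.
- Effective number per arm: 450 / 1.145 = 393.0.
- Power of the two-proportion test at that number: 83.8%, against 84% stated.

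The figure reproduces. It rests on events taken primarily from hospital and provincial records, so the morbidity definition does not affect it.

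**2. Which arm has which source.**

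| Possible source of morbidity | Intervention | Control |
|---|---|---|
| Biosensor readings | daily during monitoring | none |
| Symptom questions on the tablet | daily during monitoring | none |
| Pre- and poststudy surveys | yes | yes |
| Hospital and provincial records | yes | yes |

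The two empty cells are an inference. The article never states outright that control patients have no sensors. The inference rests on four statements: controls remain on usual care, telemonitoring is not standard care, the sensors and tablet are components of the intervention technology, and the platform is costed as incremental to usual care. Nothing in the article supplies the equipment to control patients.

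With pairwise allocation, 15 hospitals × 30 patients = 450 patients per arm. Sensor values are therefore available for 0 of about 450 control patients.

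**3. What follows for each possible measure.**

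- *Sensor data alone:* no control observations, so the contrast cannot be estimated.
- *Sensor data pooled with self-report:* let true morbidity be p in both arms (no treatment effect), let s be the probability that self-report picks it up, and let d be the extra detection that sensors and daily prompts add. Observed proportions are p(s + d) in the intervention arm and p·s in the control arm, so the spurious excess is p(s + d) − p·s = p·d. The document gives neither p nor d. With assumed values:
  - p = 0.10, d = 0.05: 0.10 × 0.05 = 0.005, or 0.5 percentage points.
  - p = 0.20, d = 0.10: 0.20 × 0.10 = 0.02, or 2 points.
  - p = 0.30, d = 0.20: 0.30 × 0.20 = 0.06, or 6 points.

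  These show how the bias arises. They do not estimate its size.
- *Survey self-report alone, or records alone:* the same source applies to both arms, and this problem does not arise.

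**The case against.** The strongest reply is that no between-arm comparison of sensor data is written anywhere. The morbidity clause sits in a paragraph shared by both studies and fits Study 1 as it stands. The comparisons between arms that the article does describe are the primary-outcome model and the cost and utilization comparison. Monitoring data go to process control charts, which describe patients over time. This stands. A reader might infer that the plan prescribes a biased contrast, or that telemonitoring would be made to look harmful because it detects more; the document supports neither. But the charts do not rescue the outcome, because a description of monitored patients cannot show a reduction against usual care, which is what the outcome list promises.

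Second, the clause also names self-report, and both arms complete surveys. This stands in part. A reader might suppose that controls offer only one recall at 90 days, but they also complete the prestudy survey. The surveys described under Study 1 include SF-8 health-related quality of life, self-care and utilization, so a comparable self-reported measure with a baseline is available. The article does not make it the morbidity measure, and the stated source still includes sensors.

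Third, Data Collection Procedures leaves outcomes open to refinement after the feasibility study. That makes a correction easy but is not itself one. The feasibility study, with no control group described, would not expose the problem.

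Fourth, an article may leave details to a fuller document. The point here is a source that the article names and that fails in the controlled design, not a missing detail.

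Finally, the volume of one-sided data might be taken as the size of the problem: up to 450 × 60 = 27,000 patient-days, or 450 × 30 = 13,500 under the one-month monitoring period in Data Collection Procedures. That counts readings. It does not measure bias.

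**Conclusion.** The point holds, with moderate weight. As stated, the Study 2 morbidity outcome relies partly on a source that only the intervention arm can supply. The sensor component cannot be compared between arms, and combining it with self-report would ascertain morbidity more intensively in the intervention arm. The asymmetry is clear from the text; the size of any bias is unknown.

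The conclusion assumes that usual care provides no TEC4Home equipment, which the article implies consistently but does not state in so many words.

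A reader might go further and conclude that the trial's main result is at risk. It is not. Morbidity is one secondary item. The primary outcome rests on records available in both arms and its power reproduces. Utilization, mortality, quality of life and patient experience do not depend on sensors.

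**What to change.** In Study 2, Process and Outcome Measurement, separate the morbidity outcome from the Study 1 wording and make two changes before hospitals begin enrolling:

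1. Define morbidity for the RCT only from sources collected identically in both arms. Options are the common pre- and poststudy survey (for example SF-8 health status at follow-up, adjusted for baseline), hospital or provincial records (for example days in hospital to day 90), or both. Name the chosen measure.
2. State that sensor readings and tablet symptom reports are descriptive, intervention-arm-only data, analysed with the process control charts already planned, and that no between-arm claim will be drawn from them.

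**Cost.** Mainly wording, since both surveys and records are already to be collected in both arms. The article speaks of visits and admissions, so the team should confirm that length of stay will be extracted if hospital days are chosen. The morbidity outcome loses its physiological detail. A records-based version partly overlaps the primary outcome; outcomes restricted to heart-failure-coded visits and admissions would overlap it more, and the article does not show that such coding will be obtained. A survey-based version avoids most of that overlap but depends on patients returning the poststudy survey.

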#### Data Collection Procedures

Both control and intervention patients will complete pre- and poststudy period surveys as described in Study 1. The ultimate primary and secondary outcomes will be subject to further development and refinement as necessary by the project team as informed by the feasibility study. Patient screening and training to use the TEC4Home system will occur as in the feasibility study. Patients will be monitored at home for one month during which data will be collected daily from the patient station biosensors (eg, blood pressure) and self-reported health indicators (eg, dizziness). Pre- and postintervention surveys will be administered to patients, recording social demographics and QoL as measured by the PROM and PREM tools. Postsurveys will include self-report items related to health system utilization including family physician visits, emergency department visits, and lab work.

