#### Procedures and Data Collection

Eligible patients will be invited to consent once stabilized in the emergency department. Measures and tools will be administered in order for patients to assess the research process and to inform Study 2. A prestudy survey will be administered to patients that includes social demographics, health related QoL as measured by a Patient-Reported Outcome Measure (PROM) (ie, Short Form Health Survey, SF-8) [20], patient activation (ie, Patient Activation Measure, PAM-13) [21], self-care and management (ie, European Heart Failure Self-Care Behavior Scale, EHFScBS-9) [22], health care utilization, and patient attitudes towards technology. Health care utilization and patient attitudes towards technology will be assessed by instruments developed and/or adapted by the study team. Patients will receive training and be equipped with the TEC4Home system prior to discharge from the emergency department. Patients will be monitored at home for 60 days with technical support and data will be collected from biosensors and patient self-reported health status twice daily. Thirty days after the 60-day monitoring period (ie, 90 days later), each patient will be administered a poststudy survey including the QoL, patient activation, self-care and management, health care utilization, and attitudes towards technology components of the prestudy survey in addition to items related to end-user experience including satisfaction with the TEC4Home experience and usability, perceived value, willingness to pay for this type of service/equipment based on an estimated cost provided to them in the survey, and relative value of components of the service. End-user experiences will be assessed using the System Usability Scale [23], while patient satisfaction and experiences will be assessed using survey tools developed by the research team. Patients across both sites will be invited to take part in individual interviews to help investigators firmly understand their experiences using TEC4Home and to provide in-depth information to illustrate, explain, and account for outcomes.

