#### Analysis

Hospital data captured and analyzed to assess outcomes will include patient revisits and admission rates within the 90 days postdischarge from the emergency department (60 days of monitoring and 30 days of additional follow-up) and days saved. Regression analysis will be used to analyze the impacts of age, gender, ethnicity, living circumstances, and attitudes towards technology on the outcomes. Individual level administrative data for heart failure patient revisits to emergency department and admission will be reviewed. Costs per patient for equipment, set-up, connectivity, and monitoring will be calculated and included in the analysis.

Content analysis of patient and health professional interviews will be used to identify themes and resulting recommendations for quality improvement of both implementation and evaluation processes to inform Study 2.

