#### Analysis

We will use descriptive analysis to compare baseline characteristics of emergency departments and individuals. For the primary analysis, an intent-to-treat hierarchical (mixed-effects) logistic regression model will be fit to compare the proportions of patients who experienced the primary outcome in the intervention and control arms. This model will adjust for baseline characteristics at both the emergency department (eg, prestudy emergency department revisit/hospitalization rate, service area population) and patient (eg, age, gender) level. As hospital records will supply emergency department revisit/hospital admission data, missed outcome events will be rare. Monitoring data will be analyzed using statistical process control charting techniques to allow a more comprehensive understanding of patient’s health condition over time.

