### Study 3: Innovation Testing (Months 20-38)

During the trial period, a concurrent but separate test study will be conducted. This will entail the recruitment and engagement of an additional emergency department site during an 18-month period. The purposively selected site will be an emergency department in the Metro Vancouver area that is not involved in the cluster RCT (ie, Study 2). The innovation study will compare usual monitoring protocol to the same protocol with the addition of Sentrian intelligent monitoring software.

The goal of this study is to determine the value of the Sentrian innovation and demonstrate the value of this system to health professionals. Given the numbers of heart failure patients presenting in the emergency department in this setting over 18 months and the eligibility criteria, we expect approximately 135 patients would be eligible to enroll. Note that inclusion/exclusion criteria are the same as in the previous two studies. A minimum 60% consent rate yielding a sample size of approximately 80 patients is estimated with a maximum attrition rate of 15%. Patients will be randomized into one of two groups as they present to the emergency department: (1) regular monitoring or (2) monitoring plus Sentrian intelligent monitoring software. This innovation study is not about the outcome of revisits or admissions; rather the purpose is to determine how best to measure utilization and health professional experience in terms of decision support (that is, how the information provided by the Sentrian technology alters the physicians’ decision processes). Therefore the purpose is not to develop a model for clinical suggestions but rather to test the impact of Sentrian predictive model on physicians’ clinical decisions for this patient population. Because this study is not designed for a definitive comparison, no power calculation has been included. The primary outcome for this study will be health care utilization and will be measured by patient self-reporting as well as administrative data during the full 90-day follow-up (60 days monitoring, 30 days additional tracking). We will also collect health professionals’ perspectives around how this innovation impacted decision support.

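### Study 2 gives two lengths for home monitoring: one month in Data Collection Procedures, 60 days elsewhere in the same study

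*Protocol article*

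**What the plan says.** The Study 2 text gives the monitoring period in three places.

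- Data Collection Procedures: "Patients will be monitored at home for one month during which data will be collected daily from the patient station biosensors".
- Process and Outcome Measurement, in the definition of the 90-day primary outcome: "60 days of which the patient will be monitored".
- Intervention and Control Population, on what happens after each Health Authority's 18-month trial period: an "additional total 90 days of monitoring (60 days) and follow-up (30 days").

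The other two studies in the article use 60 days plus 30. Study 1 says "Patients will be monitored at home for 60 days with technical support" in Procedures and Data Collection, and "60 days of monitoring and 30 days of additional follow-up" in its Analysis section. Study 3 measures utilization "during the full 90-day follow-up (60 days monitoring, 30 days additional tracking").

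Study 2 also states two uses for the data collected during monitoring. One is a secondary outcome, "reduction in morbidity as tracked through patient sensor data and self-report". The other is in the Analysis section: "Monitoring data will be analyzed using statistical process control charting techniques".

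**The concern.** One month and 60 days cannot both be the monitoring period of the same trial. The text does not present one month as a minimum, as a sub-period of the 60 days, or as a deliberate change from the feasibility study. The same paragraph says that screening and training follow the feasibility study, which monitored for 60 days.

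The intervention is the monitoring, so its length is the dose. The outlying figure stands in the procedures section, where a site would look to learn how long to keep a patient on the system. Thirty hospitals start in monthly steps by Health Authority, and two stated durations leave room for practice to differ between sites. At stake are the length of the intervention actually delivered, the length of each patient's sensor record, and the incremental platform cost that enters the cost-effectiveness evaluation.

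**Working it through.** **1. Statements of monitoring duration**

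| Study | Section | Monitoring | Follow-up after it |
|---|---|---|---|
| 2 | Data Collection Procedures | one month | not given |
| 2 | Process and Outcome Measurement | 60 of 90 days | remaining 30 days implied |
| 2 | Intervention and Control Population | 60 days | 30 days |
| 1 | Procedures and Data Collection | 60 days | 30 days |
| 1 | Analysis | 60 days | 30 days |
| 3 | Innovation Testing | 60 days | 30 days |

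One month appears once; 60 days appears in every other row. The 3-month program described under Pilot Project Findings is the earlier Ministry/TELUS pilot and supports neither value.

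**2. Fit to the 90-day outcome window** (one month taken as 30 days)

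- 60 + 30 = 90 days, which fills the window.
- 30 + 30 = 60 days, which leaves 90 − 60 = 30 days unaccounted for.

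**3. Size of the discrepancy**

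- Share of the window monitored: 30/90 = 33% against 60/90 = 67%.
- Ratio of the two durations: 30/60 = 0.5.
- Readings per patient, at one a day with full adherence: about 30 against 60.
- Outcome days without sensor data: 90 − 30 = 60 against 90 − 60 = 30. Days 31 to 60 are the ones in dispute.

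**4. Does the sample size depend on it?**

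Inputs from Power and Sample Size: 12% against 6%, 30 hospitals with 30 patients each (450 patients per arm), intraclass correlation 0.005, two-sided alpha 0.05.

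- Design effect: 1 + (30 − 1) × 0.005 = 1.145.
- Effective number per arm: 450 / 1.145 = 393.
- Standard error under the alternative: √[(0.12 × 0.88 + 0.06 × 0.94) / 393] = √(0.162 / 393) = 0.0203.
- Power with unpooled variance: Φ(0.06/0.0203 − 1.96) = Φ(0.995) = 84.0%.
- Power with pooled variance under the null: null standard error √(2 × 0.09 × 0.91 / 393) = 0.0204, so Φ[(0.06 − 1.96 × 0.0204)/0.0203] = Φ(0.984) = 83.8%.

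The stated 84% reproduces. Monitoring length is not an input, so the calculation is the same under either duration.

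**The case against.** The strongest reply is that this is an editorial slip. A reader of the whole article can recover 60 days, and the primary outcome, the sample size and the mixed model stay as they are. That is true. It limits the seriousness but does not remove the contradiction, which concerns the length of the intervention and stands in the section that governs conduct.

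Three further points have force.

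- **The direct support for 60 days within Study 2 is thinner than the table suggests.** The text on intervention and control hospitals describes the run-out of departments after enrolment closes, so it implies a per-patient duration without defining one. The explicit per-patient statement is the parenthesis in the outcome definition. Study 2 also departs from Study 1 in collecting data daily where Study 1 collects twice daily, so a deliberate change of duration cannot be excluded from Study 1 alone. This is why the sponsor needs to confirm.
- **The harm from a shorter sensor series is modest.** Control hospitals stay with usual care, and the article does not say that their patients receive sensors. Sensor-tracked morbidity therefore looks like intervention-arm data at either duration, and the control charts are descriptive. The effects on dose and platform cost are the more tangible ones.
- **An unchanged power calculation does not mean that duration is irrelevant to power.** The assumed fall to 6% comes from the Ministry/TELUS pilot, which ran as a 3-month program. Whether that effect would hold with one month of monitoring is open, and the article gives no figure from which to quantify it.

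That a journal article condenses the full protocol is no answer here. Condensing explains an omission, whereas this text states two incompatible values.

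**Conclusion.** The concern holds. Study 2 is internally inconsistent on how long patients are monitored, and the one-month figure is the outlier. If followed, it would halve the monitoring period and the daily series (30 against 60 days; about 30 against 60 readings) and would leave 60 rather than 30 of the 90 outcome days without sensor data. These counts assume a 30-day month, one submission a day and full adherence.

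The 90-day primary outcome, the planned 900 patients, the mixed model and the 84% power figure are calculated without reference to the duration and stand as written. The point should be fixed before sites start, but it is not a threat to the primary analysis. That 60 days is the intended value is an inference from the other statements; the article does not declare it.

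**What to change.** In Study 2, Data Collection Procedures, replace one month with 60 days, after the sponsor confirms that 60 days is the intended monitoring period. Leave the daily collection and the rest of the sentence as they are. If the sponsor instead intends one month, the outcome definition and the 60 + 30 split in the section on intervention and control hospitals must change to match.

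The recommended change costs one phrase and one confirmation. The outcome, sample size and analysis are untouched.
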